## Study outcomes and risk factors

The main study outcomes are clinical (mortality, morbidity and relapse of malnutrition) and nutritional (weight, height, MUAC, leg length, head circumference, mid-thigh circumference, skin-fold thickness and body composition by bioimpedance vector analysis) assessed over 48 weeks of follow-up. Mortality is assessed in hospital by daily physician review and, post discharge, through study visits and by telephone where possible for children who are lost to follow-up. Morbidity during hospitalisation is assessed through daily clinical assessments and available hospital laboratory tests. Morbidity after discharge is assessed, first, using daily morbidity diaries, in which caregivers record episodes of illness (lethargy interfering with feeding; respiratory distress; diarrhoea; oedema and fever); second, from caregiver recall and review of handheld medical records at each follow-up visit; and, third, from data collected during hospitalisation for children who are readmitted during the follow-up period. Time-to-recovery from malnutrition will be evaluated during hospitalisation; relapse of malnutrition during follow-up will be categorised as moderate acute malnutrition, uncomplicated SAM and complicated SAM, according to WHO definitions. Nutritional outcomes will be expressed both as continuous variables (attained Z-score and change in Z-score between visits), and as categorical variables (moderate wasting, WHZ<–2; severe wasting, WHZ<–3; stunting, HAZ<–2; severe stunting, HAZ<–3; underweight, WAZ <–2; and microcephaly, head circumference-for-age <–2).

Risk factors will be evaluated at baseline, hospital discharge and over the period of follow-up for associations with clinical and nutritional outcomes. In addition to baseline clinical and demographic factors, the following laboratory parameters will be evaluated: haemoglobin, serum albumin, C reactive protein (CRP), CD4 count and HIV viral load (for HIV-positive children). Haemoglobin, CD4 and HIV-viral load will be measured in real time and the results reviewed during follow-up clinics.

Data on potential confounders are collected at baseline, discharge and during the follow-up period, including child feeding practices, household socioeconomic status (defined by household income and cooking method), maternal employment and education, and household factors such as water, sanitation and hygiene practices, availability of electricity, location (rural, peri-urban or urban) and household size.

## Analysis

All analyses will be interpreted exploratively since HOPE-SAM is an observational study with multiple risk factors, outcomes and substudies. For all analyses, p values will not be artificially adjusted, but interpreted as exploring the strength of evidence supporting any association. The only exception is the use of approaches to minimise false discovery when analysing high-dimensional data from the microbiota and metabolomics substudies, as described.

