### Eligibility for microbiota and metabolomics substudies

Children enrolled into the enteropathy substudy are also included in the microbiota and metabolomics substudies since these substudies use the stool, urine and plasma samples collected for enteropathy analyses.

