Using stored samples, a longitudinal series of investigations will compare gastric and small intestinal barrier function, using a range of biomarkers to capture the domains of malnutrition enteropathy (online supplementary table 2). To understand better the extra-intestinal consequences of enteropathy, we will first compare the microbial composition of the upper gut and plasma using deep sequencing in a subgroup of children with paired gastric and blood samples. Second, we will undertake transcriptomics using PAXGene blood samples to determine (i) whether there are differences in gene expression profiles between well-nourished controls, HIV-negative children with SAM and HIV-positive children with SAM (including comparison of oedematous and non-oedematous types); and (ii) whether specific patterns of gene expression are associated with morbidity and mortality in SAM.

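### The one exception to unadjusted p values covers only microbiota and metabolomics, so the enteropathy substudy's whole-blood transcriptomics falls outside false-discovery control

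*Protocol article*

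**What the plan says.** The opening paragraph of the Analysis section sets a general rule: "For all analyses, p values will not be artificially adjusted, but interpreted as exploring the strength of evidence supporting any association". It then names one departure: "The only exception is the use of approaches to minimise false discovery when analysing high-dimensional data from the microbiota and metabolomics substudies". The same paragraph gives all analyses exploratory status: "All analyses will be interpreted exploratively since HOPE-SAM is an observational study with multiple risk factors, outcomes and substudies".

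The transcriptomics is described under Substudies, Enteropathy substudy: "we will undertake transcriptomics using PAXGene blood samples to determine (i) whether there are differences in gene expression profiles between well-nourished controls", HIV-negative SAM and HIV-positive SAM, including a comparison by oedema. A second aim is to find "whether specific patterns of gene expression are associated with morbidity and mortality in SAM". The same paragraph plans to "compare the microbial composition of the upper gut and plasma using deep sequencing in a subgroup of children with paired gastric and blood samples".

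The false-discovery text appears in two other places, both headed microbiota and metabolomics: once under Sample sizes, where the purpose given is to limit false positives, and once under Analysis, where Benjamini-Hochberg is attached to microbial taxa, microbial genes and metabolites. The eligibility section for these two substudies says that "these substudies use the stool, urine and plasma samples collected for enteropathy analyses". PAXgene blood is not in that list.

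**The concern.** Expression profiling measures very many features per child. That is the situation in which unadjusted p values mislead most, and presumably why the article makes an exception for the metagenomic and metabolomic data. The wording grants the exception by substudy, not by type of data, so a dataset of the same kind in a different substudy is left out.

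This is more than missing detail. Had the article been silent on multiplicity for transcripts, the matter could be left to an analysis plan. But it says that the rule holds for all analyses and that there is one exception. An analysis plan that controlled false discovery for transcripts would depart from the published rule, and one that followed the rule would leave them uncontrolled. At stake is how far genes reported as differing by HIV status, oedema or nutritional status, or as linked to death, can be relied on when choosing pathways for later work.

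**Working it through.** **Which data the exception reaches**

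| Data | Substudy in the article | False-discovery control stated? |
|---|---|---|
| Stool metagenomics | Microbiota | Yes |
| Urine and plasma metabolites | Metabolomics | Yes |
| PAXgene whole-blood transcriptomics | Enteropathy | No |
| Gastric and plasma deep sequencing | Enteropathy | Not by name; arguable |

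The enteropathy part of the Analysis section does not bring transcripts back in. It describes t-tests on continuous outcomes, with p<0.05 triggering a regression model, and has no false-discovery step.

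**Size, if transcripts are tested singly**

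The article states no figure to reproduce. Inputs: m, the number of transcripts, is assumed, with 5,000 to 20,000 as the main range. The threshold of 0.05 is borrowed from the enteropathy analysis of continuous outcomes, because none is given for transcripts.

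With no true difference:
- Expected false positives per contrast = 0.05 × m. For m = 5,000: 250. For 10,000: 500. For 20,000: 1,000.
- For independent tests, P(at least one) = 1 − 0.95^m. This reaches 99% at m = ln(0.01)/ln(0.95) = 89.8, so about 90 tests, and is 1.0000 to four decimals from m = 1,000 upwards.
- A simulation of t-tests on 100 v 100 children (60 runs; blocks of 100 genes, correlation 0.5) gave means of 245, 605 and 998 for 5,000, 12,000 and 20,000 genes. These agree with 0.05 × m = 250, 600 and 1,000.

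**Sensitivity to correlation** (m = 10,000, no true difference, 2,000 replicates)

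| Correlation between genes | P(at least one), p<0.05 | Mean false | Median false | P(any), Benjamini-Hochberg q = 0.05 |
|---|---|---|---|---|
| Independent | 1.000 | 500 | 500 | 4.4% |
| 100 blocks, 0.5 | 1.000 | 501 | 497 | 4.5% |
| 20 blocks, 0.8 | 1.000 | 505 | 457 | 1.6% |
| 5 blocks, 0.8 | 0.995 | 514 | 230 | 1.7% |
| One common factor, 0.5 | 1.000 | 514 | 188 | 2.2% |
| One common factor, 0.8 | 0.79 | 489 | 12 | 1.8% |

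The mean stays near 500 throughout. Strong correlation makes the count uneven: in the last row half the replicates have 12 or fewer, while the 95th percentile is about 2,995.

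**Sensitivity to threshold** (independent tests). At p<0.001, m = 1,000 gives 1 expected false positive and P(at least one) = 63%; m = 10,000 gives 10 and 99.995%.

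**When some genes do differ.** If m0 of the m genes are null, 0.05 × m0 false positives are still expected and are added to the true ones. The false share of the list then depends on how many genes differ and on power. Nothing in the unadjusted rule limits it.

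**The case against.** The best defence is that the article sets no decision rule for transcripts. It speaks of expression profiles and patterns, which may mean multivariate methods. It treats p values as graded evidence, and it gives no gene count or gene-level threshold. The p<0.05 trigger was written for continuous outcomes compared by t-test, and 100 v 100 was planned for the lactulose-mannitol ratio and inflammatory markers. All of that stands, and it makes the size above conditional. The exploratory label, however, does not justify the exclusion: the microbiota and metabolomics analyses are equally exploratory and still receive false-discovery control.

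It can also be said that this is a condensed article and that the exception may only summarise the methods it goes on to describe. That may be how the sentence arose, but its wording closes the list and should be corrected.

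A reader might infer three stronger things that the document does not support:
- **That false genes are certain to be declared.** This needs a gene count, single-gene testing and a threshold that the article does not state. Under extreme correlation, P(at least one) fell to 0.79.
- **That any resulting gene list or pathway would be pure chance.** This holds only if no gene differs at all. The Pathogenesis of SAM section cites consistent evidence of altered immune mediators, so a complete null for SAM against controls is not the expected case, and unadjusted p values would still rank genes.
- **That the gastric and plasma sequencing is excluded just as clearly.** It is microbial composition data from children who are also in the microbiota substudy, so it can be read as covered by that analysis, although gastric samples are not in that substudy's specimen list. The gene-level figures do not apply to it.

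**Conclusion.** The point holds as a fault in the scope of one sentence. As written, the multiplicity rule leaves the whole-blood transcriptomics unadjusted, and no other section restores control. Confidence in that reading is high.

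The consequence is conditional. It assumes single-transcript testing at unadjusted p<0.05 and 5,000 to 20,000 transcripts, none of which the article states for these data. On those terms, 250 to 1,000 false positives per contrast are expected when nothing differs, and the planned contrasts are several (nutritional status, HIV, oedema, morbidity, mortality). With real effects the harm is an uncontrolled share of false genes among true ones. The matter should be corrected, but it does not touch the cohort's clinical comparisons or the low-dimensional biomarkers.

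**What to change.** Reword the exception in the opening paragraph of the Analysis section so that it is defined by type of data: false-discovery control applies to all high-dimensional data. Name the enteropathy substudy's transcriptomics and, to remove doubt, its gastric and plasma sequencing where taxa are tested individually. State that Benjamini-Hochberg is applied across all measured features within each contrast, and give the level. Keep unadjusted p values for low-dimensional outcomes.

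This is one sentence and needs no new samples or data. With q = 0.05 in the simulations above, the chance of declaring any gene when none differs falls to between 1.6% and 4.5%. The price is shorter gene lists and less sensitivity for individual genes. Unadjusted p values can still be reported alongside for ranking.

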### Observational cohort

The primary comparison will be the clinical and nutritional outcomes of children with HIV-SAM compared with HIV-negative children with SAM. We will review all deaths and adjudicate clinical diagnoses and causes of death to ensure robust and consistent data across sites. We will compare each participant’s clinical management to WHO guidelines to identify any contributory factors in hospital care. Factors associated with outcomes during hospitalisation (eg, mortality, nutritional recovery) will be determined for each group (HIV-SAM and HIV-negative children with SAM) using multivariable analysis (Cox models for time-to-event data, linear models for continuous outcomes). Factors associated with outcomes over 48 weeks post discharge (hospital readmission, morbidity and mortality, relapse, anthropometry, body composition and response to ART) will be determined for each group (HIV-SAM and HIV-negative children with SAM) using multivariable analysis (Cox models for time-to-event data, linear models for continuous outcomes). HIV-positive children with SAM and HIV-negative children with SAM will be included in one model together with the risk factors, and interaction tests will be used to investigate whether associations between risk factors and outcomes differ between the two groups of children. We will evaluate the ability of MUAC at discharge to predict long-term outcomes using receiver-operator-characteristic (ROC) analysis, in the whole cohort and within the subgroups of HIV-SAM and HIV-negative children with SAM. We will then evaluate whether addition of other variables improves the predictive capacity of MUAC (using WHO criteria in those >6 months, and published data for children <6 months^62^) for each group, including body composition, haemoglobin, albumin and CRP, plus CD4%, viral load and timing of ART initiation (HIV-SAM only). We will construct multivariable models and compare them with MUAC alone using the net-reclassification index.

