## Introduction

Malnutrition underlies almost half of all childhood deaths in developing countries.^1^ Severe acute malnutrition (SAM) is defined by a weight-for-height Z-score (WHZ) <–3, mid-upper arm circumference (MUAC) <115 mm and/or bilateral pitting oedema.^2^ Current treatment guidelines distinguish two groups: (i) children with uncomplicated SAM who can be managed in the community and (ii) children with complicated SAM, who are hospitalised and undergo resuscitation, stabilisation and nutritional rehabilitation. In-hospital mortality in children with complicated SAM remains high despite the implementation of WHO guidelines.^3^ Furthermore, SAM presents as two major clinical phenotypes: non-oedematous SAM (marasmus), characterised by severe wasting, and oedematous SAM (kwashiorkor), a more complex syndrome characterised by bilateral pitting oedema, steatosis and diarrhoea.^4 5^ Despite differing clinical outcomes, treatment protocols are the same for both oedematous and non-oedematous SAM.

A contributory factor to high inpatient mortality is the co-occurrence of HIV infection in around one-third of children hospitalised for SAM in sub-Saharan Africa.^6 7^ While new HIV infections in children have declined,^8^ a substantial number of infected children are diagnosed late and present with malnutrition. There is also a growing population of HIV-exposed uninfected (HEU) children who have immune abnormalities, poor growth and higher risk of mortality and infectious morbidity.^9^ Hence, HIV has transformed the epidemiology and outcomes of SAM.^10^ Even with standardised treatment approaches, inpatient deaths are almost fourfold higher among HIV-positive children with SAM (herein termed HIV-SAM) compared with HIV-negative children with SAM (30.4% vs 8.4%), for reasons that remain unclear^10^; this mortality is threefold higher than would be expected from anthropometric parameters alone.^10^ Management of HIV-SAM is particularly challenging because HIV fundamentally alters the clinical presentation of malnutrition and the response to treatment. Children with HIV-SAM are more stunted and wasted; have a higher frequency of persistent diarrhoea; tend to have delayed nutritional recovery and have a more complicated clinical course than HIV-negative children with SAM.^10^

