### Discharge

The clinical team decides when the child is ready to be discharged, which is generally when their medical complications are resolving and the child has a good appetite and is clinically well and alert.^2^ Children receive ready-to-use therapeutic feeds (RUTF) to take at home according to local guidelines. At discharge, the study nurse collects data and a repeat blood sample (including full blood count) and undertakes discharge anthropometry, body composition, leg length (Zimbabwe only) and triceps, subscapular and supra-iliac skinfold thickness measurements (table 2). The caregiver is given a daily morbidity diary and pre-prepared stickers corresponding to different illnesses and shown how to complete the diary. The caregiver is provided with the date of the first follow-up appointment and contact details of the study nurse.

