## Sample sizes

### Observational study

The observational cohort will recruit as many children with SAM as possible during the period of enrolment (July 2016 to March 2018), estimated at 600–800 children (capped at 800 maximum), to assess clinical and nutritional outcomes among HIV-positive and HIV-negative children hospitalised with SAM. Assuming mortality of 15%, overall loss to follow-up of 15% and recruitment target of 800 children, there would be 560 evaluable children at 48 weeks, of whom 224 would have HIV-SAM based on an estimated inpatient HIV prevalence of 40%. This will provide >80% power to detect absolute differences of 17% in binary outcomes between HIV-SAM and HIV-negative children with SAM, and of 0.33 times the SD in continuous outcomes.

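### Cox models are named for in-hospital death with no provision for discharge alive as a competing event, so the hazard ratio would not measure in-hospital risk

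*Protocol article*

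**What the plan says.** Under Analysis, Observational cohort, the article states "Factors associated with outcomes during hospitalisation (eg, mortality, nutritional recovery) will be determined for each group" (HIV-SAM and HIV-negative), "using multivariable analysis (Cox models for time-to-event data, linear models for continuous outcomes". No third model type is named there. The next sentence treats outcomes over the 48 weeks after discharge as a separate analysis with the same two model types, so the plan divides time at discharge.

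The HIV contrast comes from two other sentences of that section: "The primary comparison will be the clinical and nutritional outcomes of children with HIV-SAM compared with HIV-negative children with SAM", and "HIV-positive children with SAM and HIV-negative children with SAM will be included in one model together with the risk factors", with interaction tests.

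On how the hospital stay ends, the Discharge section says "The clinical team decides when the child is ready to be discharged, which is generally when their medical complications are resolving". On what to expect by HIV status, the Introduction says that children with HIV-SAM "tend to have delayed nutritional recovery and have a more complicated clinical course than HIV-negative children with SAM". The section does not mention censoring, competing events or a time horizon for in-hospital death.

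**The concern.** A child in hospital leaves observation in one of two ways: death or discharge alive. Discharge is not an incidental end of follow-up. It is granted because the child is improving, and it removes the child from the risk of dying in hospital. A Cox model that censors at discharge estimates the death rate per day among those still on the ward. A factor that leaves this daily rate unchanged but prolongs the stay raises the proportion who die in hospital, and the model reports no effect. A factor that prolongs the stay at equal in-hospital mortality is reported as protective.

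The article's own interest is in risk. Its background evidence is a pair of proportions: "inpatient deaths are almost fourfold higher among HIV-positive children with SAM (herein termed HIV-SAM) compared with HIV-negative children with SAM (30.4% vs 8.4" per cent). The Objectives seek factors that independently predict outcomes, and the Discussion measures inpatient care against case-fatality percentages. At stake are the HIV contrast for inpatient death and the list of independent predictors. Both would be reported on a scale that mixes mortality with length of stay, and a reader would tend to take them as statements about who dies in hospital.

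**Working it through.** **Inputs from the article.**
- In-hospital mortality 30.4% v 8.4% (Introduction).
- "Assuming mortality of 15%, overall loss to follow-up of 15% and recruitment target of 800 children", with 40% HIV prevalence (Sample sizes, Observational study).
- Its stated figures reproduce: 800 × (1 − 0.15 − 0.15) = 560 evaluable children, and 0.40 × 560 = 224 with HIV-SAM. The same prevalence at enrolment gives 320 v 480. No figure is stated for the in-hospital Cox analysis itself.

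**Assumptions, not in the article.** Constant hazards of death and discharge, a two-sided 5% test, and the ratio of mean stays (HIV-SAM to HIV-negative). A 10-day mean stay in the HIV-negative group was used to simulate; only the ratio affects the result.

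**Formula.** Let d and a be the daily rates of death and of discharge alive.
- In-hospital risk: p = d / (d + a)
- Mean stay: L = 1 / (d + a)
- Hence d = p / L
- Cox HR with discharge censored = (p₁/L₁) / (p₀/L₀) = risk ratio ÷ stay ratio

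**With the article's own risks.** Risk ratio = 30.4 / 8.4 = 3.62. Dividing by 1, 1.5 and 2 gives HR 3.62, 2.41 and 1.81. The HR reaches 1.00 only at a stay ratio of 3.62.

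**Simulation** (320 v 480 children, 5,000 runs per row; HR from the formula):

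| In-hospital risk, HIV-SAM v HIV-negative | Stay ratio | Cox HR | Cox test rejects | Test of proportions rejects |
|---|---|---|---|---|
| 30.4% v 8.4% | 1 | 3.62 | 1.00 | 1.00 |
| | 1.5 | 2.41 | 0.998 | 1.00 |
| | 2 | 1.81 | 0.88 | 1.00 |
| 20% v 11.7% | 1 | 1.71 | 0.82 | 0.89 |
| | 1.25 | 1.37 | 0.40 | 0.89 |
| | 1.5 | 1.14 | 0.11 | 0.89 |
| 15% v 15% | 1 | 1.00 | 0.05 | 0.05 |
| | 1.25 | 0.80 | 0.22 | 0.05 |
| | 1.5 | 0.67 | 0.58 | 0.05 |

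The second and third risk pairs are illustrative. Both average 15% overall (0.4 × 20% + 0.6 × 11.7% = 15%), the article's planning mortality, which it does not split into in-hospital and later deaths.

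A subdistribution-hazard analysis, which keeps discharged children in the risk set, behaves like the test of proportions. It rejects in 0.87 to 0.89 of runs for 20% v 11.7% and about 0.05 for equal risks. For 30.4% v 8.4% its ratio barely moves with stay (4.13, 4.07 and 4.05 at stay ratios 1, 1.5 and 2).

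The algebra is not specific to HIV. It applies within each HIV group to any risk factor that changes length of stay.

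**The case against.** **The article never says discharge is censored.** This is correct. A reader might infer that ordinary censoring is a stated rule, but it is an inference from two facts: Cox is the only named model that fits death, and time is split at discharge. Censoring rules are often left to the full protocol or SAP, neither of which is shown. What remains is that the article itself fixes the model class for a main outcome, and that class does not give in-hospital risk without a further provision.

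**A cause-specific Cox model is legitimate.** Also correct. In the equal-risk rows the daily death rates really differ, so the rejections are not false positives for that rate. A reader might infer that the model invents or misses an HIV effect; it does so only if the HR is read as in-hospital risk.

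**The size is assumed.** The article gives no length of stay. It says recovery is delayed, and it ties discharge to resolving complications, appetite and general condition rather than to full nutritional recovery. Higher mortality also shortens stay. With 30.4% mortality, a doubled mean stay needs the daily discharge rate to fall from 0.916/10 = 0.0916 to 0.696/20 = 0.0348, about 2.6-fold. A reader might infer that the HIV effect could come out null or reversed. With the article's own risks that is not shown within a stay ratio of 1 to 2.

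**The lead sentence concerns factors within each HIV group.** True. The HIV contrast rests on the primary-comparison and joint-model sentences, and the algebra covers both uses.

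**All analyses are declared exploratory.** This lowers the weight of rejection rates. It does not change what the estimate measures.

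**Conclusion.** The point holds in a limited form. The article names Cox for in-hospital mortality and makes no provision for discharge alive, although discharge depends on recovery and recovery is expected to be slower in HIV-SAM. If children are censored at discharge, the HR is a valid daily death rate among those still admitted, but it is not a measure of in-hospital risk.

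Over an assumed stay ratio of 1 to 2, the cited risk ratio of 3.6 would appear as an HR between 3.6 and 1.8. The difference would usually still be detected. The vulnerable findings are smaller risk differences and individual predictors: at a stay ratio of 1.5, a risk ratio of 1.71 becomes an HR of 1.14, and equal risks become 0.67. These sizes rest on constant hazards and an unknown stay ratio; the article supports only the likely direction. This is a worthwhile improvement to the plan, not proof that its HIV comparison would fail.

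**What to change.** In Analysis, Observational cohort:

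1. Make the main analysis of in-hospital death a risk-scale one. Use multivariable logistic regression, as the Immunology substudy analysis already does for infectious mortality during hospitalisation, or a subdistribution-hazard model with discharge alive as the competing event. State how transfers and self-discharges are counted, since the article does not describe them.
2. Add all-cause death from admission to one fixed horizon, without censoring at discharge. Study outcomes and risk factors already provides for vital status after discharge through visits and telephone contact. Children lost to follow-up would still be censored.
3. Keep the cause-specific Cox HR as a secondary analysis, labelled as a daily death rate among children still admitted.
4. Apply the same rule to the within-group risk factors and to the joint HIV model.

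The cost is a change of wording and one extra model on data already being collected. The downside is that hazard ratios for in-hospital death move to a secondary role.
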